### Outcome measures and outcome assessment

The primary outcome will be the domain “activities of daily living” from the Stroke Impact Scale (SIS). This will be used to measure the individuals’ levels of participation. As secondary outcome measures, the other domains from the SIS will be used, as well as their total score and the percentage of recovery from stroke, for the purpose of measuring the range of structures/functions and activities. These will be measured using the Montreal Cognitive Assessment (MoCA), Berg Balance Scale (BBS), 6-minute walk test (6MWT), 10-meter walk test (10MWT), and Timed Up & Go Test (TUG).

All measurements will be carried out by trained evaluators who will not be involved in the interventions and will be blinded to the allocation of individuals to the groups. All individuals will be evaluated at three moments: before the beginning of the interventions (baseline), immediately after the end of the interventions (posttest), and 1 month after the end of the interventions (follow-up). The schedule of enrollment, allocation, and postallocation is provided in Table 1.

**Table 1 Tab1:** Outcomes assessment time-points and instruments

	Instruments/methods	Enrolment	Baseline	Allocation	Post allocation	
					Post test 15 weeks	Follow up 19 weeks
Eligibility screen: Socio-demographic variables	Structured interview, recording age, brain injury, schooling and medical history	X				
Informed consent	Informed Consent Term	X				
Allocation	3 intervention groups: RMG, VMG or CMG			X		
Quality of life	SIS		X		X	X
Cognitive	MOCA		X		X	X
Gait Functional Capacity	6MWT		X		X	X
Self-selected gait speed	10 MWT		X		X	X
Mobility	TUG		X		X	X
Balance	Berg Balance Scale (BBS)		X		X	X

### Intervention

The intervention for the three sample groups will be 15 weeks long and will consist of two weekly sessions of 60 min each. All interventions will be carried out at the School of Physical Education and Sports of the University of Sao Paulo, Brazil.

The individuals allocated to RMG will carry out sessions in multimodal training in a real environment. The sessions will be divided into four moments, based on guidelines from Billinger et al. [26]: balance and cognition (15 min in duration), training of the aerobic component and muscular strength (20 min each), and a fourth moment focused on flexibility and relaxation (5 min in duration). Aerobic circuits, games, adapted sports, strength training stations, tasks with varying bases of support, double tasks, memorization tasks, and other strategies will be used. Materials will include balls of diverse sizes and constitutions, dumbbells, washers, cones, hula hoops, bladders, wooden sticks, mats, shuttlecocks, and rackets.

Individuals assigned to the VMG group will carry out individualized multimodal training sessions in a virtual environment. For this protocol, there will be eight games of Stability and Balance Learning Environment, a system of virtual reality developed by Motekforce Medical (Amsterdam, the Netherlands), which is composed of a 10.76-ft^2^ force platform, three projectors, six infrared cameras, a sound system, and a touchscreen panel for selection and control of variables. The games of this virtual reality device were produced and adapted to be beneficial for special populations that have balance and movement disorders, such as people with neurological disorders (stroke, cerebral palsy, Parkinson’s disease, traumatic brain injury), orthopedic disorders (amputees, osteoarthritis, musculoskeletal disorders), and the geriatric population (elderly with increased risk of falling). Stability and Balance Learning Environment requires the player to move the entire body, which includes tasks of reach, stationary gait, and others.

These games were grouped into two blocks of sessions that will be applied alternately throughout the intervention. The odd sessions (Fig. 2) will include the games balloon pop, city ride, hit the mole, and 2d maze, and the even sessions (Fig. 3) will consist of the games road encounters, road stepping, paper flight, and hit knees. The number of selected games as the group session in two models aims to make the most motivating interventions possible and keep the characteristics between the games of both models similar.

**Fig. 2 Fig2:**
[figure not shown]
Virtual reality games selected for the odd-game sessions and individuals’ practice

**Fig. 3 Fig3:**
[figure not shown]
Virtual reality games selected for the even-game sessions and individuals’ practice

In order to guarantee the multimodal character of the virtual intervention and to make it similar to the real intervention, the games were classified according to the perceptual and motor demands of the virtual reality systems protocol developed by Cairolli et al. [27]. The use of this classification protocol ensured that the games placed similar demands on the individuals. For example, the demand for strength and cardiovascular resistance could be consistent across the selected games.

Finally, individuals in the CMG group will perform an intervention that combines the protocols of the two other groups described above. In this way, one of the weekly sessions will be held in a real environment and the other in a virtual environment.

Before the start of all sessions, regardless of the group, the individuals’ blood pressure will be verified in order to ensure that no one initiates the practice of physical exercise with a blood pressure greater than 160/105 mmHg [28]. This contributes to the safety of the practice. To register and control the data, stethoscopes (Efficacy line, Bunzl Saúde, Brazil) and manual blood pressure cuff aneroid sphygmomanometers (Solidor, Bunzl Saúde, Brazil) will be used.

Aerobic exercise intensity control will be performed to ensure the safety of the interventions in the three groups. During the interventions, the individuals’ heart rate (HR) will be monitored constantly in order to keep it aligned with the range prescribed individually using the Karvonen formula ((HR_maximum_ − HR_rest_) × percentage HR intensity + HR_rest_) [29]. We will use 40% and 70% of the reserve HR, as determined by Billinger et al. [26], as the lower and upper intensity thresholds, respectively. The maximum HR will be calculated using the formula 220 − age in years [30], except in individuals who use beta-blockers. Thus, the maximum HR will be calculated by the formula 164 − 0.7 × age in years [31]. For the control of HR ranges, we will use Polar brand H7 frequency meters synchronized with the Polar Team application (Polar, Bethpage, NY, USA). As a complementary form to intensity control, we will use the Borg Rating of Perceived Exertion [32, 33], which correlates with the objective measures of the workload level and HR [24]. The individuals’ perception of effort will be verified before the beginning of each session and soon after the onset of the aerobic component in the real environments, or soon after the practice of each of the games in the virtual environment sessions. We will adjust the offer of stimuli that indicate perceptions between values 11 and 14, as determined by Billinger et al. [26].

Resistance exercise intensity will also be controlled according to Billinger et al. [26]. All individuals will perform eight to ten exercises, preferably involving the major muscle groups. Each exercise will include 1 to 3 sets of 10 to 15 repetitions.

Every 5 weeks, the aerobic and resistance exercise intensity will be adjusted in terms of progression. By the end of the 15-week intervention period, we will have performed two progressions. The aerobic component will include gradual increases (10%) of the HR percentage, and the resistance component will increase through larger numbers of sets or repetitions for each exercise.

### Measurements

*Quality of life* will be evaluated through the SIS. This scale evaluates quality of life by measuring 59 items categorized in 8 domains: strength (4 items), hand function (5 items), activities of daily living/instrumental activity of daily living (10 items), mobility (9 items), communication items [7], emotion (9 items), memory and reasoning (7 items), and participation function (8 items). Each item is rated on a 5-point Likert scale in terms of difficulty the patient has experienced in completing each item. Summative scores will be generated for each domain, ranging from 0 to 100. An extra question will be asked in order to know, on a scale from 0 to 100, how much the individual feels they have recovered since their stroke. Our primary outcome measure will be the domain of the activities of daily living/instrumental activity of daily living, and the rest of the domains will be used as secondary outcome measures [34]. The Brazilian version of SIS 3.0 has satisfactory internal consistency, test-retest reliability, convergent validity, and discriminant validity in stroke patients [34]. SIS 3.0 is a specific measure of psychometrically robust HRQoL that can be useful in assessing the consequences of stroke in different cultural contexts [34]. For some of the domains that make up this scale, there are values of minimum detectable change (MDC) and clinically important difference (CID). According to Lin et al. [35], the values are strength (MDC 24.0 and CID 9.2), activities of daily living/instrumental activities of daily living (MDC 17.3 and CID 5.9), mobility (MDC 15.1 and CID 4.5), and hand function (MDC 25.9 and CID17.8).

*Cognition* will be evaluated through the MoCA. MoCA was developed as an instrument of rapid screening for mild cognitive dysfunction and for evaluating different cognitive domains, such as attention and concentration, executive functions, memory, language, constructional visual skills, conceptual thinking, calculations, and logical reasoning. The scale ranges from 0 to 30 [36]. In the chronic phase of stroke, MoCA has a good correlation with other short cognitive tests and shows high sensitivity and specificity in the prediction of post-stroke cognitive deterioration [37]. There is no consensus on the cutoff to define cognitive impairment for stroke, but most authors use a 26-point cutoff. There are no MDC values for this scale [38]. For the subacute phase of stroke, the scale shows excellent internal consistency (α = 0.78) [39].

*Balance* will be evaluated through the BBS, which organizes the quantitative description (classification of 0 to 4) of functional balance ability into 14 items common to daily life. It has a minimum score of 0 and a maximum of 56 [40]. The measurement’s MDC is 4.66 [41], and it has excellent test-retest reliability (intraclass correlation [ICC] = 0.98) [42].

*Gait functional capacity* will be evaluated through the 6MWT, which quantifies the maximum distance, expressed in meters, that the individual is able to walk in 6 min [43]. The measurement’s MDC is 36.6 m [44]; the CID is 34.4 m [45]; and it has excellent test-retest reliability (ICC = 0.99) [44].

*Self-selected gait speed* will be evaluated through the 10MWT, which determines the average speed, expressed in meters per second, that the individual applies for a distance of 10 m. The measurement CID is 0.06 m/s [46], and it has excellent test-retest reliability (ICC = 0.94) [44].

*Mobility* will be evaluated through the TUG, which determines the time, expressed in seconds, that the individual takes to perform a task involving a change of direction, transfer, and gait [47]. The measurement’s MDC is 2.9 s, and it has excellent test-retest reliability (ICC = 0.96) [44].

### Statistical analysis

It was estimated that a sample of 36 participants (12 per group) would provide 88% power (α = 5%) to detect a difference between group means of 17.3 (MDC of the activities of daily living/instrumental activities of daily living domain of the SIS) using the program G*Power 3 [48], which takes into account the number of sample groups and the number of evaluation measures. To reach this total number of individuals, at least 43 individuals must be recruited, allowing a dropout rate of 20%.

For the mathematical treatment and statistical analysis of the data, Excel software (Microsoft, Redmond, WA, USA) will be used for the tabulation of data, and SPSS version 13 software (SPSS, Chicago, IL, USA) will be used for statistical analyses. A significance level of 5% will be adopted. Initially, for the characterization of the sample, descriptive analysis and the *t* test will be used to examine differences between the RMG, VMG, and CMG groups. Subsequently, for the analysis of the normality and homogeneity of the results of the primary outcome measure and secondary outcomes, the Shapiro-Wilk and Levene tests will be used, respectively. After observing the assumptions for normality and homogeneity, parametric analysis will be performed using two-way analysis of variance (3 groups by 3 moments [baseline, post-test, and follow-up]) and post hoc Tukey test. The mean between-group difference and 95% confidence intervals will be reported for all outcomes. If any subject gives up the protocol, their measured outcomes will be analyzed on an intention-to-treat basis.

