**Methods/design:**

We will conduct a randomized clinical trial with three groups: a real multimodal group (RMG), a virtual multimodal group (VMG), and a combined multimodal group (CMG). It was estimated that we will need a sample of 36 participants (12 per group). RMG individuals will only perform multimodal physical exercises in a real environment two times per week for 60 min per session for 15 weeks. VMG individuals will perform exercises of the same duration over the same time frame but only in a virtual environment. CMG individuals will hold a weekly session in a real environment and another weekly session in virtual environment. The primary outcome measure will be health-related quality of life, evaluated using the Stroke Impact Scale; effects on cognition (Montreal Cognitive Assessment), balance (Berg Balance Scale), mobility (Timed Up & Go), self-selected gait speed (10-meter walk test), and gait functional capacity (6-min walk test) will be investigated as secondary outcome measures. Participants will be evaluated before the beginning of the intervention, immediately after the end of the intervention, and at 1-month follow-up without exercise. If the data meet the assumptions of the parametric analysis, the results will be evaluated by analysis of variance (3 × 3) for the group factor, with repeated measures while taking into account the time factor. The post hoc Tukey test will be used to detect differences (α = 0.05).

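### Minor arithmetic error: recruiting 43 leaves about 34 participants, not 36, after the 20% dropout the plan allows for; the figure should be 45

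*Protocol article*

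**What the plan says.** The sample-size paragraph is in the Statistical analysis section of the protocol article. Its basis is the claim that 36 participants, 12 in each of three groups, "would provide 88% power (α = 5"%) "to detect a difference between group means of 17.3" points on the activities-of-daily-living domain of the Stroke Impact Scale. The next sentence makes the allowance for losses. It says that, to arrive at those 36, "at least 43 individuals must be recruited, allowing a dropout rate of 20"%. The Methods/design part of the abstract repeats the 36: "It was estimated that we will need a sample of 36 participants (12 per group").

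So 36 is the number to be left after dropout, and 43 is the minimum to be recruited. No formula for the step from 36 to 43 is given.

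**The concern.** An allowance for dropout has to be taken as a share of those recruited, because they are the people who can drop out. Adding 20% of the required number is not the same as recruiting enough to lose 20% and still have the required number. The printed 43 looks like the first calculation used for the second purpose.

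If so, the recruitment minimum does not deliver the analysed sample on which the power statement rests, under the dropout rate the plan itself assumes. At stake is the internal consistency of the sample-size paragraph and a small amount of power.

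**Working it through.** **Inputs**, all from the Statistical analysis section: required number after dropout n = 36; assumed dropout d = 0.20; stated recruitment minimum 43; stated power 88% at n = 36; α = 5%.

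**1. Reproducing the stated figure.** n × (1 + d) = 36 × 1.20 = 43.2, which is 43 to the nearest whole number. This matches the article. Rounding up, as is usual for sample sizes, would have given 44.

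**2. The number that meets the stated aim.** n / (1 − d) = 36 / 0.80 = 45 exactly. Check: 45 × 0.80 = 36. Rounding does not explain the gap, since the division gives a whole number and even 44 leaves only 44 × 0.80 = 35.2.

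**3. What 43 delivers.** 43 × 0.80 = 34.4 expected completers, which is 36 − 34.4 = 1.6 short.

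**4. The dropout that 43 can absorb.** (43 − 36) / 43 = 7/43 = 16.3%.

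**5. Effect on power.** The article prints no standard deviation, standardised effect or correlation between repeated measures, so the 88% cannot be rebuilt from its inputs. It is taken as given here, and only the relative loss is computed. For each F test in a 3 × 3 repeated-measures analysis, the noncentrality λ is solved so that power is 88% at N = 36. It is then scaled by 34/36, and the denominator degrees of freedom are recalculated: N − 3 for groups, 2(N − 3) for time and for the interaction.

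| Test | df at N = 36 | λ at N = 36 | λ × 34/36 | df at N = 34 | Power at N = 34 |
|---|---|---|---|---|---|
| Between groups | 2, 33 | 13.04 | 12.32 | 2, 31 | 85.8% |
| Time | 2, 66 | 12.44 | 11.75 | 2, 62 | 85.9% |
| Group × time | 4, 66 | 15.61 | 14.74 | 4, 62 | 85.7% |

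As a cross-check, a comparison of two means differing by 17.3 has 88% power with 12 per group if the standard deviation is about 13.5 (a back-solved value, not one from the article). With 34/3 per group its power is 86.1%. All four routes give about 86%, a loss of about two points.

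**The case against.** The strongest reply is that the error is too small to matter: two recruits and about two points of power, with the outcome, analysis and interpretation unchanged. That stands as a judgement of weight. It does not make the sentence correct.

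Two further replies mitigate only in part.

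- **Intention to treat.** The article says that the measured outcomes of anyone who gives up the protocol will be analysed on this basis. A participant who stops exercising but still attends assessment therefore need not be lost. This does not help with participants who have no post-test measurement, and the article names no imputation. The plan's own inflation step also treats dropout as lowering the usable number.
- **A minimum, not a cap.** The wording sets 43 as a floor, so recruiting 45 is permitted. The floor is still too low for the dropout rate attached to it.

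A reader might infer more than the article supports:

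- **That the trial is materially underpowered.** The figures show a relative loss of about two points from an 88% that cannot be verified here. They say nothing about the trial's true power.
- **That the authors multiplied by 1.2.** This fits, but it is inferred. What can be shown is only that 43, 36 and 20% are inconsistent.
- **That 43 is wrong because it does not divide by three.** The 12 per group describes the required 36, and the Randomization procedures section promises neither blocking nor equal numbers recruited.
- **That the chance of reaching 36 is the measure of harm.** With each participant independently having an 80% chance of completing, the binomial probability of at least 36 completers is 35% from 43 recruits and 59% from 45. But 45 also misses 36 about 41% of the time. An allowance for dropout plans for the expected number, so this contrast adds little.

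**Conclusion.** The sentence is wrong as written, and the error is minor. Under the plan's own 20% dropout, 43 recruits leave about 34 participants rather than 36, and reaching 36 in expectation takes 45. The shortfall is two recruits (45 − 43). This conclusion uses only the printed 36, 43 and 20%.

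The power figure of about 86% is conditional. It assumes that 88% is right at 36, that the effect and variance assumptions stay the same, and that those who drop out contribute nothing to the analysis. If some dropouts are still assessed, the loss is smaller.

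**What to change.** Correct the sentence so that the recruitment figure is 36 / (1 − 0.20) = 45, with the formula shown.

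If recruitment stays at 43, keep that number and restate what it supports: about 16% dropout for 36 completers; at 20% dropout, about 34 completers and power of about 86% rather than 88%, on the same assumptions. This may be the realistic option, since the Trial status section expected recruitment to finish in the first half of 2019 and dates the proof review 27 May 2019.

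Either way the cost is one corrected sentence, plus two more recruits under the first option or a slightly lower stated power under the second. The required 36 in the abstract can stay as the target after dropout under the first option.

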### Randomization procedures

Participants who meet the study inclusion criteria will be randomized into one of three sample groups—the real multimodal group (RMG), the virtual multimodal group (VMG), or the combined multimodal group (CMG)—through a draw of numbered (generated by computer) and sealed opaque envelopes. The evaluators have no knowledge of the results of the individual allocation (blinded evaluators). However, the same is impossible to perform with the professionals who will perform the interventions; because the interventions are supervised and progressive, there are clearly distinct protocols between groups of individuals.

To characterize the individuals, the Mini Mental State Examination, Fugl-Meyer Assessment, and Orpington Prognostic Scale will be applied. The individuals will also be characterized by the demographic variables of sex, age, type of stroke, injury time, affected brain hemisphere, and schooling.

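### A two-group t test is named for comparing three randomised groups at baseline; the tests should be dropped in favour of a descriptive table

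*Protocol article*

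**What the plan says.** The Statistical analysis section of the protocol article sets one significance level for everything: "A significance level of 5% will be adopted". The first analysis step serves to characterise the participants. It combines descriptive statistics with a t test, and the article says that this "test will be used to examine differences between the RMG, VMG, and CMG groups". No other test and no multiplicity correction is named for this step. For the outcomes, the same paragraph plans a three-group method: a two-way analysis of variance (three groups by three moments) with a post hoc Tukey test.

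The design has three arms: "We will conduct a randomized clinical trial with three groups". The planned size is 12 per group.

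The section on randomization procedures lists what characterises the participants. There are three scales ("the Mini Mental State Examination, Fugl-Meyer Assessment, and Orpington Prognostic Scale will be applied") and six further items ("demographic variables of sex, age, type of stroke, injury time, affected brain hemisphere, and schooling"). Allocation is by computer-generated numbers in sealed opaque envelopes.

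**The concern.** The named test cannot do what the sentence asks. A t test handles two groups, so a comparison of three becomes three tests per variable, and as written each is run at 5%. The outcome analysis in the same paragraph does use a three-group method with a multiple-comparison procedure, so the two steps do not match.

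There is a more basic difficulty. If the randomisation was carried out properly, any difference between arms at baseline arose by chance. A p-value for it then tests a hypothesis already known to be true, and says nothing about whether an imbalance is large enough to matter for the outcome.

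At stake is the reading of the baseline table. Chance differences marked as significant may cast doubt on a sound randomisation. Differences not marked may be taken as harmless when, in groups of 12, they need not be.

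**Working it through.** **Inputs from the protocol article.** Three groups, 12 per group, 5% level, no correction stated. Nine characterisation variables. Six are non-categorical: the Mini Mental State Examination, Fugl-Meyer, Orpington scale, age, injury time and schooling. Three are categorical: sex, type of stroke and affected hemisphere.

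**Assumptions.** Tests are two-sided (not stated), t tests use pooled variance with 12 + 12 − 2 = 22 degrees of freedom, there are no true differences (randomisation), and variables are independent of each other.

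**Step 1. The plan's own figure.** The only figure for this step is the 5% level. In 200,000 simulated null trials with three groups of 12 and a normal variable, a single pairwise t test rejects in 4.95%. The level holds for each test taken alone.

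**Step 2. Per variable.** Three groups give three pairs.
- If the three tests were independent: 1 − 0.95³ = 14.3%.
- The pairs share groups, so the true figure is lower. The simulated chance of at least one significant pair is 12.1%.
- One omnibus F test on the same simulated data rejects in 4.9%.

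**Step 3. Over the six non-categorical variables.** The chance of at least one false flag is 1 − (1 − p)⁶.
- Pairwise t tests: 1 − (1 − 0.1213)⁶ = 1 − 0.460 = 54%.
- Omnibus tests: 1 − 0.95⁶ = 1 − 0.735 = 26%.
- Expected number of variables flagged: 6 × 0.121 = 0.73, against 6 × 0.05 = 0.30.

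**Step 4. Sensitivity.**
- Skewness: for a strongly skewed (lognormal) variable the any-pair rate is 9.0%. If all six behaved that way, the overall figure would be 1 − (1 − 0.0899)⁶ = 43%.
- Dependence: correlation between variables lowers the 54%. In the limit where all six move together it falls to the single-variable 12%.
- All nine variables, if the categorical ones were t-tested too: 69% counting each at 12.1%, or 70% treating three as binary with assumed prevalences of 0.5, 0.5 and 0.8. Omnibus tests would give 1 − 0.95⁹ = 37%.

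**Step 5. What the test misses.** With 12 per group a pairwise t test is significant only if the observed difference exceeds 2.074 × √(2/12) = 0.85 pooled SD. Its power is 22% against a difference of 0.5 SD and 47% against 0.8 SD.

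**The case against.** **The step is only descriptive.** It is introduced as characterising the sample. No covariate choice, exclusion, change of model or check on randomisation in the article hangs on its result, and the 3 × 3 analysis runs the same way whatever it shows. This stands, and it limits the severity.

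**Categorical variables.** A reader might infer that sex, stroke type and hemisphere will be t-tested, because they are among the characterisation variables and no other test is named. The text pairs descriptive analysis with the t test and does not say which variables get which. Those three may only be described, or a condensed article may have left out a chi-square test. The inference is therefore unsupported, and so is a headline of nearly 70% that depends on counting all nine variables. The three-group error does not need it.

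**How much is due to the t test.** Omnibus tests would still flag something in 26% of trials over six variables. About half of the 54% therefore comes from testing baseline at all. This also stands. It argues for dropping the tests rather than exchanging them.

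**A correction could be applied.** Pairwise t tests can be corrected for multiplicity. That is true, but the article states none here, and the result would still be a test of chance differences.

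**Baseline is already in the model.** The outcome analysis includes baseline as one of three moments. That is so, which means that using it as a covariate changes the model and is more than a wording edit.

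**Conclusion.** The point holds and is minor. As written, a two-group test at an uncorrected 5% is assigned to a three-group comparison. Run pairwise with 12 per group, it raises the false-flag rate for a normal variable from 5% to about 12%. Over six non-categorical variables, about 54% of trials would show at least one false flag, against 26% with omnibus tests. These figures rest on two-sided pooled t tests, normal data and independent variables. Skewness or correlation would lower the totals, while the mismatch between test and design would remain.

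The effect is confined to the baseline table. A reader might go further and conclude that the primary comparison is compromised, or that the plan will choose covariates from these p-values. The article ties no such decision to them.

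**What to change.** Delete the baseline t tests. Report baseline by group descriptively: mean and SD, or median and interquartile range for skewed variables, with counts and percentages for sex, stroke type and hemisphere. This is a wording change and removes analysis work. Replacing the t test with analysis of variance or chi-square tests would lower the false-flag rate but would keep a test with no useful question behind it.

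As a separate change, state in advance that the group comparisons at post-test and follow-up are adjusted for the outcome's own baseline value as a covariate, whatever imbalance is seen. This deals with chance imbalance in the outcome's own baseline without reference to any p-value. The cost is small but is more than wording: the outcome model must be restated with post-test and follow-up as the responses and baseline as a covariate, instead of baseline as one of three repeated moments. The baseline outcome values are already scheduled for collection, so no new data are needed.

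### The primary ANOVA is conditional on Shapiro-Wilk and Levene tests of the trial's own data, with no decision rule or named alternative, so the primary analysis is not fixed in advance

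*Protocol article*

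**What the plan says.** The Abstract (Methods/design) makes the main analysis conditional: "If the data meet the assumptions of the parametric analysis, the results will be evaluated by analysis of variance". No otherwise follows.

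The Statistical analysis section describes the procedure. For normality and homogeneity of the primary and secondary outcomes, "the Shapiro-Wilk and Levene tests will be used, respectively". Then: "After observing the assumptions for normality and homogeneity, parametric analysis will be performed using two-way analysis of variance", with three groups, three moments and a post hoc Tukey test. On the level of testing it says only "A significance level of 5% will be adopted", without tying this to the assumption tests.

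The section does not say how many assumption tests are run, whether each is run per group, per visit or on residuals, or whether a single rejection rules out the ANOVA. No transformation, rank test or other method is named anywhere in the article. The same section promises mean between-group differences and 95% confidence intervals for all outcomes, without condition.

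**The concern.** A trial's primary analysis should be settled before the outcome data are seen. Here its use depends on significance tests of those same data, and the other branch is empty. If a test rejects, someone must choose a method with the results in view.

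The tests are also weak guides at this size. With 12 per group they have little power against moderate departures from normality, yet several run together will often reject when nothing is wrong. The primary measure, the activities of daily living domain of the Stroke Impact Scale, is bounded at 0 and 100; the Montreal Cognitive Assessment and the Berg Balance Scale are bounded too. Skew or ceiling effects are plausible, so the question is likely to arise in practice.

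What is at stake is chiefly the estimate. A rank test, the usual move after a failed normality check, does not yield the mean difference that the plan promises. The unconditional promise and the conditional analysis cannot both be relied on.

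**Working it through.** **The plan's own figures.** The article gives no figure for how often the assumption tests would fail. Its one related figure, 88% power for a 17.3-point difference, cannot be reproduced because no SD or correlation is stated. A pairwise normal approximation needs an SD of about 13.5: 17.3 / (13.5 × √(2/12)) = 3.14; 3.14 − 1.96 = 1.18; Φ(1.18) = 0.88. That figure is not used below.

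**Inputs from the Statistical analysis section.** 12 per group, 3 groups, 3 moments (9 cells), 5% significance level.

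**Assumptions, because the article is silent.** Each assumption test is at 5%; any one rejection counts as failure; the between-visit correlation r is 0, 0.5, 0.7 or 0.9; the data are exactly normal with equal variances.

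**False alarms.** For k independent tests, P(at least one rejects) = 1 − 0.95^k. The simulation used 3 groups × 12 × 3 visits, 6,000 runs for each r.

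| How the tests are applied | k | Formula | Simulated |
|---|---|---|---|
| One Shapiro-Wilk, one Levene, independent observations | 2 | 9.75% | 9.7% (r = 0) |
| Post-test only: 3 Shapiro-Wilk, 1 Levene | 4 | 18.5% | 18.1% to 18.8% |
| One of each per visit | 6 | 26.5% | 22% to 30% |
| 9 cell-wise Shapiro-Wilk only | 9 | 37.0% | 31% to 35% |
| 9 cell-wise Shapiro-Wilk, 3 Levene | 12 | 46.0% | 46.6%, 46.3%, 45.7%, 38.7% (r = 0, 0.5, 0.7, 0.9) |

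With the median-centred form of Levene's test the last row becomes 36% to 42%.

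The lowest figure needs independent observations. If all three visits were pooled into one test of each kind and their correlation ignored, simulated failure rose to 18.8%, 31.9% and 53.6% at r = 0.5, 0.7 and 0.9. That is a misuse of the tests, so it is left out of the range, but the text does not exclude it.

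**Misses.** With an assumed skewness of 1 and 12 observations, a single Shapiro-Wilk test rejects about 17% of the time, so it misses 100% − 17% = 83%.

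**Type I error.** The fallback is assumed to be Kruskal-Wallis in place of ANOVA on the change from baseline to post-test, triggered by any of the 12 tests, at r = 0.7 and 4,000 runs per scenario. Under the null the error was 5.6% for normal data, 4.6% for skewed data and 4.4% for ceiling-limited data; a further run with normal data gave 4.4% to 5.4%. The simulation error is about 2 × √(0.05 × 0.95 / 4,000) = 0.7 percentage points, so these values are compatible with 5%. Always taking the smaller of the two p-values gave 5.5% to 6.4%.

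**The case against.** The strongest reply is that this is a condensed article. The fallback method, the unit tested and the diagnostic rule are details commonly left to a full protocol or SAP, neither of which is shown, and the ANOVA, its factors and the post hoc test are stated. That stands as far as the missing fallback alone is concerned: its absence here does not show that none exists. It does not answer the main point. The article commits to choosing the analysis by tests of the trial's own outcomes, and that rule would be poor even if an unseen document named the alternative.

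Three stronger readings are tempting, and the objection to each is sound.

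- A reader might infer that about 45% of trials with normal data would fail. That needs all 12 tests, 5% for each, and an any-rejection rule. The article states none of these, and other readings it allows give much lower figures.
- A reader might infer that a rejection blocks the primary analysis. The text does not say that the ANOVA is dropped, or that nothing is run. It leaves the next step undefined.
- A reader might infer that the type I error rate is out of control. How often the tests reject is not a false-positive rate for the treatment comparison, and the simulated switch hardly moved the error. A wider choice of methods could do more, but that has not been shown.

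It would also be wrong to fault the plan for testing raw scores rather than residuals. The article does not say which is tested, and Shapiro-Wilk is unaffected by a shift in location, so within a single cell the two give the same result.

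Finally, the loss of the promised estimate is a possibility, not a certainty: no rank test is named, and rank methods have location-shift intervals. Such an interval is still not one for the mean difference.

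**Conclusion.** The point holds in limited form. The Abstract and the Statistical analysis section both make the primary parametric analysis conditional on preliminary tests, without a decision rule or a named alternative. The primary method is thus open to choice after the data are seen, and the promised mean differences and 95% CIs are not secured.

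The size can only be given as a range. Normal, equal-variance data would fail in about 10% to 47% of trials, depending on how the tests are applied, on the assumptions of 5% per test and failure on any rejection. No reading examined makes a false alarm negligible.

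The defect is an unfixed primary analysis and estimate. It is not a demonstrated large inflation of error: about 5% to 6% for one assumed fallback and one contrast. It does not invalidate the trial, but it should be corrected.

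**What to change.** Delete the condition in the Abstract and in the Statistical analysis section, and state that one analysis is run whatever the assumption tests show.

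- **Analysis.** Replace the 3 × 3 ANOVA, which treats baseline as an outcome level, with a baseline-adjusted comparison of the groups: ANCOVA, or a mixed model, with the baseline score of the SIS activities of daily living domain as covariate. The plan does not contain this model at present, so it has to be written in.
- **Estimates.** Report the mean differences and 95% CIs from that model, so that the existing promise is met by the primary analysis itself.
- **Diagnostics.** Inspect residuals graphically, as description and not as a rule for choosing the method.
- **Sensitivity.** Name one analysis of the same contrast: a permutation test or a bootstrap CI.

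The cost is wording and one additional analysis. Recruitment, visits and data collection do not change.
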